## **2.0 STUDY OBJECTIVES**

### **2.1 Phase I**

#### **2.1.1 Primary Objectives**

- Assess safety of the no-flip technique for Shang Ring circumcision in males aged 10 years and older

#### **2.1.2 Secondary Objectives**

- Assess ease of use of the Shang Ring with the no-flip technique
- Evaluate satisfaction of the no-flip Shang Ring among study participants
- Evaluate satisfaction of using the no-flip Shang Ring technique among MC providers
- Determine the occurrence and safety of spontaneous detachment
- Evaluate acceptability of wearing the Shang Ring for more than 7 days following circumcision

### **2.2 Phase II**

#### **2.2.1 Primary Objectives**

- Compare pain experienced during the Shang Ring circumcision procedure with topical vs. injectable anesthesia. EMLA Cream (lidocaine 2.5% and prilocaine 2.5%) will be the topical anesthetic used and the injectable anesthetic will be 1% lidocaine, the standard currently used in the Kenya National VMMC program.

#### **2.2.2 Secondary Objectives**

- Compare safety of topical vs. injectable anesthesia for local anesthesia during Shang Ring circumcision
- Compare ease of use of topical vs. injectable anesthesia for local anesthesia during Shang Ring circumcision
- Explore service optimization for use of topical anesthesia in conjunction with Shang Ring circumcision
- Compare duration of post-procedural analgesic effects between the topical vs. injectable anesthesia groups
- Compare satisfaction with the topical vs. injectable anesthetic among study participants

- Compare satisfaction with the topical vs. injectable anesthetic among circumcision providers

## 3.0 ENDPOINTS

### 3.1 Phase I

#### 3.1.1 Primary Endpoints

- We will address the primary objective by evaluating the rate of moderate and severe adverse eventsi (AEs) following Shang Ring MC using the no-flip technique based on clinical exam findings. Other safety endpoints will include documentation of time to complete clinical wound healing,ii device-related malfunctions and occurrences of device displacement.

#### 3.1.2 Secondary Endpoints

We will address the secondary objectives by evaluating the following endpoints:

- To evaluate ease of use with the no-flip technique we will document MC procedure and device removal times and problems encountered during MC and removal procedures;
- To evaluate satisfaction with the no-flip technique and the acceptability of wearing the Shang Ring for more than 7 days following circumcision among study participants and as appropriate their parents/LAR, we will interview participants/parents/LARs to document acceptability and satisfaction with the Shang Ring circumcision, procedure and post-procedure pain, and time to return to normal activity; and
- To evaluate satisfaction among MC providers we will interview providers to document experiences with use of the no-flip technique, problems encountered during MC procedures, and preference of MC technique.
- To determine the occurrence and safety of spontaneous detachment we will gather data on timing of spontaneous detachment and document problems/AEs and time course of complete clinical wound healing at clinical examination, as well as problems/complaints reported during interviews of participants (and as appropriate parents/LARs) among those participants wearing the Shang Ring for more than 7 days after circumcision

### 3.2 Phase II

#### 3.2.1 Primary Endpoints

- The outcome metric for the primary outcome will be maximum pain reported to have been experienced by participants during the Shang Ring circumcision, assessed using the visual analogue scale (VAS), reported immediately after completion of the Shang Ring circumcision procedure

---

i AEs will be defined in the study manual of operations and will be based on those found in the report of the January 2013 meeting of the WHO Technical Advisory Group on Innovations in Male Circumcision, as well as those being used in ongoing pilot implementation studies of PrePex, another male circumcision device being studied in Africa.

ii Complete clinical wound healing is defined as intact epithelium (unbroken skin) covering the wound as judged by the provider on visual inspection, meaning that none of the following are present: scabbing, drainage, moisture, gaps between epithelial edges or ulceration.

### 3.2.2 Secondary Endpoints

- To compare safety of the two anesthetic techniques we will document rates of moderate and severe AEs, device-related malfunctions, occurrence of device displacement, and time to complete clinical wound healing
- To compare ease of use of the topical vs. standard injection technique for local anesthesia during Shang Ring circumcision, we will document dwell time required for onset of adequate anesthesia with the topical cream and time to adequate anesthesia with injectable anesthesia, potency of anesthesia provided by both techniques, and problems encountered during anesthesia with the two techniques.
- We will also explore service optimization in terms of determining how to best sequence and group patients for Shang Ring circumcision given the dwell time necessary for topical anesthetic effect.
- To compare duration of post-procedural analgesic effects between the topical vs. injectable anesthesia groups, we will document reported pain at various time points such as 1 and 24 hours post-circumcision between the two groups using the VAS.
- To compare satisfaction with topical vs. injectable anesthetic, we will interview study participants and their parents or legally acceptable representative (LAR) as appropriate to document acceptability and satisfaction with the circumcision, the Shang Ring procedure, post-procedure pain, and time to return to normal activity between the two techniques
- To compare satisfaction with the topical vs. injectable anesthetic among clinical providers in the study, we will interview them about their experiences, acceptability and satisfaction with the two anesthetic techniques

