### **8.3 Post-Op Follow-Up Visits**

Scheduled follow up shall be conducted for a maximum of 42 days in both phases of the study, although the follow-up schedule will differ as noted below. If needed, weekly visits after Day 42 will continue until complete healing is documented in both phases.

Phase I: Participants will be asked to return to the study site for follow up on days 7, 14, 21, 28, 35, and 42. However if a client is healed on an earlier visit, e.g. day 21, his participation in the study will be completed at that time. There will be a clinical exam at each follow-up visit and an interview with the participant and/or his parent/LAR.

Phase II: Participants will be asked to return for two follow-up visits on days 7 and 42 post-circumcision. Given that we will have just completed 200 no-flip Shang Ring circumcisions with intensive follow-up as well as the data from our other previous Shang Ring vs. conventional MC RCTs using the standard Shang Ring technique, we will ask participants to return for only one follow-up visit after ring removal, at 42 days

following the circumcision procedure. We have no reason to believe that the type of anesthesia used for the circumcision procedure should have any impact on the course of healing or other outcomes after removal of the device on day 7.

The informed consent form will explain to participants that we may take photographs of their penis at various points during the preparation for and completion of the Shang Ring circumcision or device removal, or at one or more follow-up visits. However we will always ask the participants and parent/LAR as appropriate for permission immediately before taking any photographs, and participants will not be discontinued from the study if permission is not granted to proceed with photography. We intend to take photographs of the circumcision and removal procedures, of participants that may incur an AE and at follow-up visits to document wound healing.

At follow-up visits, clinical outcome measures will include adverse events and early post-surgical complications. These include the following:

- pain,
- excessive bleeding,
- problems with the delayed healing (understood herein as being beyond 42 days),
- swelling or hematoma,
- damage to the penis (e.g. injury to the glans or urethra),
- infection,
- problems with the appearance of the penis/poor cosmetic results,
- torsion,
- erectile dysfunction,
- problems with voiding,

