### 9.2 Analysis Plan Summary

A detailed analysis plan that covers both the final analysis and the planned interim analyses will be developed and reviewed and approved internally prior to initiation of the analysis. The following is a summary of the planned analyses for the two phases. Any deviations to be made from this summary plan will be documented in the detailed analysis plan.

In Phase I, the frequency and percentage of men with procedure-related AEs will be tabulated by severity, both overall and by site. Listings of AEs will include information on duration, outcome, severity, and relation to study procedures. Listings of any serious adverse events will also be provided. Shang Ring circumcision and removal procedure data (e.g. time of circumcision and removal, problems encountered, ring sizes used) will be descriptively summarized. Data on operative and post-operative pain, time to return to normal activity, participants' opinions of the Shang Ring procedure and participants' satisfaction with the post-circumcision cosmetic results will be descriptively summarized. Time to complete wound healing will be evaluated using a Kaplan–Meier estimator.

As Phase II is a randomized study of acceptability and safety, primary analyses will be conducted using an as-treated approach (i.e., depending on anesthesia method actually received). However, any deviations between the as-treated approach and a strict intention-to-treat approach will be presented to allow for the assessment of potential biases. Some secondary analyses on safety endpoints may be repeated using an intention-to-treat approach, as relevant.

VAS pain scores will be compared between randomization groups to estimate the efficacy of anesthetic technique at the time of surgery. The frequency and percentage of men with AEs will be tabulated by randomization group, relation to study procedures, and by severity, both pooled across sites and separately within each site. The analysis of AEs will include information on duration, outcome, and relation to study procedures. Stratification by severity will also be considered.

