All other endpoints will be summarized by anesthetic technique and compared between groups using either two-sample t-tests or chi-squared tests, as appropriate for the endpoint, all conducted at the two-sided 0.05 significance level. We will not make any adjustments for multiple comparisons. 95% confidence intervals for differences between groups will be presented. Missing data will be assumed to be missing in random fashion and ignored.

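### Phase II compares time to wound healing, but healing between days 7 and 42 is known only to a 35-day interval, so a difference in recorded days understates any true delay

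*Combined protocol and SAP*

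**What the plan says.** Section 3.2.2 lists the measures for comparing the safety of topical and injectable anesthesia. The last of them is healing time: "we will document rates of moderate and severe AEs, device-related malfunctions, occurrence of device displacement, and time to complete clinical wound healing". Footnote ii to Section 3.1.1 defines complete healing by the provider's visual inspection, so it can be dated only by a visit.

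The schedules in Section 8.3 differ by phase. Phase I: "Participants will be asked to return to the study site for follow up on days 7, 14, 21, 28, 35, and 42". Phase II: "Participants will be asked to return for two follow-up visits on days 7 and 42 post-circumcision". After that, "If needed, weekly visits after Day 42 will continue until complete healing is documented in both phases". Section 8.3 gives a reason for the thinner Phase II schedule: "We have no reason to believe that the type of anesthesia used for the circumcision procedure should have any impact on the course of healing". It also treats delayed healing as healing beyond 42 days. Section 8.4 allows unscheduled visits for complications, concerns or healing delayed past day 42.

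For Phase I, Section 9.2 says: "Time to complete wound healing will be evaluated using a Kaplan–Meier estimator". For Phase II it says only that the remaining endpoints will be "compared between groups using either two-sample t-tests or chi-squared tests, as appropriate for the endpoint", with 95% confidence intervals for the differences. A detailed analysis plan is to follow. No method for interval-censored times is named.

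**The concern.** The endpoint and the schedule do not match. A Phase II participant who heals on day 15 and one who heals on day 40 both enter the data as healed at day 42. A mean difference and confidence interval computed from those dates would be labeled as days to healing but would not measure days to healing.

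The safety comparison is what is at stake. Section 9.3 gives time to healing as one of the reasons to continue Phase II after the interim analysis, so the protocol expects the measure to be informative. A small reported difference could be read as reassurance about topical anesthesia when part of its smallness comes from the visit dates.

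**Working it through.** **The plan's own figure.** The documents give no power or sample size for healing time. The nearest stated figure is in Section 9.1: 100% power for a 1-point pain difference, SD 1.8, 2:1 allocation, two-sided 0.05. A two-sample t calculation gives 99.5% with 300 completers (100 vs 200) and 99.8% with 345 randomized, so that figure reproduces. The work below uses 100 injectable and 200 topical completers.

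**Inputs, all from Section 1.3.2.**
- Boys' no-flip pilot: mean 29.9 days, SD 7.3.
- Adult field study: 90.5% and 91.3% healed by the 35–42 day visit, taken as 91% by day 42. With SD 7.3 (my assumption) the mean is 42 − 1.34 × 7.3 = 32.2.
- Adult RCT, Shang Ring arm: mean 44.1 days, SD 12.6. The same trial found the Shang Ring about 5 days slower than surgery, hence the 5-day example.

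**Model.** Healing time T is normal, a delay is a pure shift, and each time is recorded at the first scheduled visit on or after T. With visits at days 7 and 42 and then weekly, the recorded day is 42, minus 35 if T ≤ 7, plus 7 for each of days 42, 49, 56, … that T exceeds. So

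mean recorded day = 42 − 35·P(T ≤ 7) + 7·[P(T > 42) + P(T > 49) + P(T > 56) + …].

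**Boys' pilot, no delay.** 42 − 35(0.0009) + 7(0.0487 + 0.0044 + 0.0002) = 42.34.

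**Boys' pilot, 5-day delay (mean 34.9).** 42 − 35(0.0001) + 7(0.1654 + 0.0267 + 0.0019 + 0.0001) = 43.36.

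The recorded difference is 1.0 day for a true difference of 5. Nearly all of it comes from participants pushed past day 42.

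**All three models.** The t-test columns are simulated with the recorded days. Ranges show the spread between a run of 4,000 trials and a repeat of 20,000.

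| | Boys' pilot | Field study, SD 7.3 | Adult RCT |
|---|---|---|---|
| Healing between days 7 and 42 | 95% | 91% | 43% |
| True 5-day delay appears as | 1.0 day | 1.5 days | 3.7 days |
| t-test power, 5 days | 87–88% | 95–96% | 84–85% |
| True 3-day delay appears as | 0.5 day | 0.8 day | 2.2 days |
| t-test power, 3 days | 38% | 52–53% | 43% |
| t-test power, 3 days, with Phase I's weekly visits | 89% | 89–90% | 48–50% |
| Healed by day 42, no delay vs 5-day delay | 95.1% vs 83.5% | 91.0% vs 74.4% | 43.4% vs 28.7% |
| Chi-squared power on healed by day 42, 5 days | 86% | 95% | 72% |

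With weekly visits the recorded difference would be 5.0 and 3.0 days in all three models.

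**Sensitivity.** If 91% heal by day 42 but the SD is 12.6, the mean is about 25.1. A 5-day delay then appears as 2.4 days, with t-test power of 61–62% and chi-squared power of 48%. This model also has 7.5% healed by day 7, when the ring is due for removal, so it strains the normal assumption.

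**The case against.** Much of the case on the other side is sound.

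- **Late healing is captured.** Weekly visits after day 42 date it, and that is what the protocol means by delayed healing. This stands.
- **A thin schedule was a reasoned choice.** The sponsor expects no effect of anesthesia type on healing. That justifies fewer visits. It does not justify keeping a comparison of healing times that those visits cannot measure.
- **Nothing commits the trial to a t-test on visit dates.** Section 9.2 allows a chi-squared test where appropriate and defers detail to a later plan. This stands, and it makes the repair easy. But the endpoint as named is a time, and the only methods offered ignore the interval.
- **It is one part of one secondary safety endpoint.** Correct.

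Three stronger readings are tempting, and the documents do not support them.

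- A reader might infer that nearly every healing time will be recorded as day 42. That fits the boys' pilot and the field study. Under the adult RCT it is 43%, and Section 6.1 puts half of Phase II above age 15. The documents do not settle which adult distribution applies.
- A reader might infer that a real delay would be hidden and the trial would show no difference because of its schedule. A 5-day delay is still detected with about 84–96% power in the three main models. Its size is distorted; its presence usually is not.
- A reader might infer that the Phase I Kaplan–Meier estimate is biased against the historical data. The historical visit schedules are not given, the pilot's 29.9 days may itself be visit-based, and Section 9.2 plans no test of healing time against history. Both Phase I arms share the same weekly visits.

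**Conclusion.** The concern holds in a limited form. In Phase II the size of a healing difference arising before day 42 cannot be estimated, and a difference in recorded days understates the truth by an amount that depends on an unknown healing distribution. A true 5-day delay appears as 1.0 to 3.7 days and a 3-day delay as 0.5 to 2.2 days. Power is about 84–96% for 5 days and about 38–53% for 3 days. For a 3-day delay the loss relative to weekly visits is large under the boys' and field-study models and small under the adult RCT model.

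These figures assume normal healing times, a common SD, a pure shift, visits on schedule, no unscheduled visit that dates healing earlier, and 300 completers. The SD of the field-study model is assumed, and a wider SD lowers the power, as shown. The understatement itself appears in every model tried. Pain and adverse event rates are unaffected.

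**What to change.** In Section 3.2.2 and the detailed analysis plan, replace the Phase II time-to-healing comparison with the proportion completely healed by the day 42 visit, reported as a risk difference with 95% CI. Alternatively, name an interval-censored method that uses the last unhealed and first healed visit dates. Either way, do not report a difference in mean days to healing. The proportion matches the protocol's own meaning of delayed healing.

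This costs wording only, with no new visits. It gives up a time-to-event claim that the schedule cannot support. The gain is an interpretable estimate, not power: for a 5-day delay, power is about the same under the boys' and field-study models and falls from 84–85% to 72% under the adult RCT model, because the proportion ignores how late healing after day 42 occurs. The interval-censored option keeps that information.

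For Phase I, an interval-censored estimate alongside the Kaplan–Meier curve is an optional refinement.

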men 18 years old and above have been conducted (as well as more than 650 no-flip procedures in children), suggest that the no-flip method is faster and easier and has no serious problems during or post-circumcision (Yan et al., 2010). Spontaneous detachment of the Shang Ring may be more likely following the no-flip technique compared to following the standard Shang Ring technique. A video of the no-flip technique can be watched at: <http://www.youtube.com/watch?v=MjJlQgU4HDw>.

Another potential innovation that could significantly improve the treatment paradigm for Shang Ring MC is the replacement of injectable local anesthetics with topical agents. Injected anesthesia, the current standard for Shang Ring circumcision, requires a skilled provider and is the most painful part of the procedure. Some men who fear needles may avoid circumcision, and use of a topical anesthetic would potentially improve acceptability of MC. Additionally, hypodermic needles can pose a risk to the provider. Reuse of needles and syringes is a potential source of infectious transmission, and safe disposal of needles and syringes can be problematic. Therefore, identifying an effective topical agent would significantly improve the treatment paradigm for Shang Ring MC and alleviate needle disposal concerns. In addition to being easier, topical anesthesia will likely be better tolerated when the faster no-flip technique is used.

Topical anesthesia is used with another male circumcision device, PrePex (Bitega et al., 2011, Mutabazi et al., 2012, Galukande et al., 2014). Although the mechanism of action of the PrePex Device is different, it does provide a theoretical basis for use of topical anesthesia with MC devices. Indeed, recently another new MC device, named the Unicirc was introduced with a mechanism of action is similar to the Shang Ring using topical anesthesia (see video at <https://www.youtube.com/watch?v=e3i1MlhV1ZU>). Additionally, there are some preliminary promising results from use of topical anesthesia in men and boys in China (personal communication). With application of topical anesthetic cream to the mucosal layer of the foreskin and dwell times of 15-45 minutes, adequate anesthesia to carry out circumcision is achieved. While data from China are limited and preliminary, they suggest that topical anesthesia for Shang Ring MC is worth pursuing more systematically.

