## 7.5 EMLA Cream

EMLA is an acronym representing Eutectic Mixture of Local Anesthetics. Eutectic mixtures permit higher concentrations of anesthetic to be used safely and facilitate application to the skin. EMLA is a 5% mixture of equal quantities by weight of lidocaine and prilocaine. When used separately, lidocaine and prilocaine are solid bases but when mixed in equal quantities, however, they form a mixture that results in an oil that allows for higher concentrations of anesthetic to be maintained during application and permits better absorption leading to greater potency but with reduced toxicity. This may enhance the anesthetic effect of EMLA over other topical anesthetic preparations. EMLA cream has been approved by the U.S. Food and Drug Administration since the early 1990s and is commercially available at reasonable cost in Kenya, as well as other countries in sub-Saharan Africa that have prioritized MC as an HIV prevention intervention, making it a good option for use with the Shang Ring if shown to be safe and effective.

The use of topical lidocaine, including EMLA, has historical precedent in device-driven circumcision, as reported for the PrePex and Unicirc devices (Mutabazi et al., 2013, Bitega et al., 2011. See video at <https://www.youtube.com/watch?v=e3i1MlhV1ZU>). One should note that the topical anesthetic used in the PrePex publications was not EMLA, but rather a "homemade" lidocaine cream. As studies progressed, the impractical nature of using such a cream for scale-up was recognized, and the ongoing PrePex pilot implementation studies in several sub-Saharan Africa countries are now using EMLA. The use of EMLA cream has also been extensively reported to be safe and effective in neonatal circumcision (Taddio, 2001 and American Academy of Pediatrics Task Force on Circumcision, 2012)

We will apply EMLA prior to circumcision with the Shang Ring, allowing for a dwell time of up to 45 minutes for onset of action, under an occlusive dressing. As noted below under section 8.2 we will explore time course of anesthetic effectiveness with a small

number of men at the start of Phase II to get a better sense of minimum required dwell time.

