The injectable approach shall utilize a combination of a penile and a ring block with 1% lidocaine injected with a small gauge needle. This is the standard anesthesia approach used in the Kenya VMMC program. The maximum amount of lidocaine administered will be 4.5 mg/kg. Onset of action typically requires 3 to 10 minutes. The topical approach shall consist of applying EMLA cream to the both the inside and outside surfaces of the foreskin. The anesthetic will then be allowed to dwell for up to 45 minutes for onset of action, with appropriate adjustments made based on the run-in described in the previous paragraph.

In both the injectable and topical anesthetic groups, we will test for numbness using the approach that is currently used, i.e. using blunt forceps on all of the quadrants of the penile shaft, on both the cutaneous and the mucosal sides to determine if anesthesia has taken effect. If it is determined that anesthesia has not taken effect in any participant in the topical group, we will resort to injectable anesthesia.

The Wong-Baker FACES Visual Analogue Scale (VAS) shall be used for pain assessment as we have done in our previous Shang Ring studies (Barone et al., 2011; Barone et al., 2012; Barone et al., 2013, Sokal et al., 2014).

The immediate complications of the circumcision procedure will be recorded on either an Adverse Event (AE) or Serious Adverse Event (SAE) form and may include such findings as: excessive pain, excessive bleeding, anesthetic-related complications, excessive swelling, excessive skin removal, and damage to the penis (e.g. injury to the glans or urethra). Data on procedure times and surgical difficulties, including problems with use of Shang Ring shall also be collected.

Participants will be instructed to return to the study site if they experience medical events such as severe discoloration of the penis, signs of infection (purulence), severe or increasing pain, or any other significant concern that they may have.

Study staff will contact participants or their parents/LAR if appropriate by mobile phone call and/or SMS to remind them of their next follow-up visit. All reasonable efforts will be made to contact those who do not return for follow-up visits. If necessary home visits may be resorted to especially in the case where the ring has not yet been confirmed at the site to have been removed or the client has an AE.

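### Phase II time to adequate anesthesia is unobserved for topical participants switched to injection, and the general analysis rules would summarise it mainly from those who went numb

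*Combined protocol and SAP*

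**What the plan says.** Section 3.2.2 makes onset time part of the comparison of ease of use: the study will "document dwell time required for onset of adequate anesthesia with the topical cream and time to adequate anesthesia with injectable anesthesia".

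Section 7.5 describes applying the cream, "allowing for a dwell time of up to 45 minutes for onset of action". The Phase II text of Section 8.2 repeats the limit ("The anesthetic will then be allowed to dwell for up to 45 minutes for onset of action") and allows it to be adjusted after the run-in. Numbness is tested in both groups. For the cream, "If it is determined that anesthesia has not taken effect in any participant in the topical group, we will resort to injectable anesthesia". No time is fixed for that switch.

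Section 9.2 calls its main approach as-treated, by the method actually received. It foresees intention-to-treat repeats only for some safety endpoints. All remaining endpoints are summarised by anesthetic technique and "compared between groups using either two-sample t-tests or chi-squared tests", as suits the endpoint. It adds: "Missing data will be assumed to be missing in random fashion and ignored". Kaplan-Meier is named only for Phase I wound healing. A detailed analysis plan is promised, in which departures from this summary are to be documented.

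**The concern.** For a participant switched to injection, the topical onset time is known only to exceed the time of the switch. It is unobserved because onset was slow or absent, so treating it as missing at random fails in a known direction. Moving him to the injectable group, as an as-treated rule would, also takes him out of the topical summary.

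Take three topical records: numb at 20 minutes, numb at 35 minutes, and not numb at 45 minutes and switched. The mean of the observed times is (20 + 35)/2 = 27.5 minutes. The third participant has no influence on it.

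At stake is the secondary comparison of ease of use, together with what it suggests about how long the cream needs. The shortfall grows with the share of participants in whom the cream fails.

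**Working it through.** **Stated figures.** The plan gives no figure for this endpoint. The Phase II power in Section 9.1 concerns pain. With 200 and 100 evaluable and SD 1.8, SE = 1.8 × √(1/200 + 1/100) = 0.220, and power for a difference of 1 is Φ(1/0.220 − 1.96) = 99.5%. This agrees with the stated 100% and plays no further part here.

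**Inputs from the documents.**
- Dwell limit 45 minutes (Sections 7.5 and 8.2).
- Injectable onset: "Onset of action typically requires 3 to 10 minutes" (Section 8.2); midpoint 6.5 minutes used.
- Earlier topical experience: "dwell times of 15-45 minutes" (Section 1.2).
- Evaluable participants: 300 at 2:1, so 200 topical and 100 injectable (Section 9.1).

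**Assumptions.** Failure rate f = P(onset later than 45 minutes), taken as 2%, 5%, 10% and 20%. Onset is lognormal with log-SD s of 0.35 to 0.5.

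**Success-only mean.** With z the (1 − f) normal quantile:
- uncapped mean = 45 × exp(−s·z + s²/2);
- success-only mean ÷ uncapped mean = Φ(z − s)/(1 − f).

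Example, f = 10% and s = 0.5: z = 1.2816, and the uncapped mean is 45 × exp(−0.641 + 0.125) = 26.9 minutes. The ratio is Φ(0.7816)/0.9 = 0.7828/0.9 = 0.870. The success-only mean is 23.4 minutes, 13% low.

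| f | Uncapped mean, s = 0.5 | Success-only mean, s = 0.5 | Shortfall, s = 0.35 to 0.5 |
|---|---|---|---|
| 2% | 18.3 | 17.5 | 2-4% |
| 5% | 22.4 | 20.6 | 5-8% |
| 10% | 26.9 | 23.4 | 8-13% |
| 20% | 33.5 | 26.5 | 14-21% |

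**Topical minus injectable, minutes (s = 0.5).** M is the success-only mean.
- By randomised group, counting the wait plus the injection: (1 − f)·M + f·(45 + 6.5) − 6.5.
- Switched participants dropped: M − 6.5.
- Switched participants moved to injectable, clock running from cream application: M − [100 × 6.5 + 200f × 51.5]/(100 + 200f).

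At f = 10% these are 0.9 × 23.4 + 0.1 × 51.5 − 6.5 = 19.7; 23.4 − 6.5 = 16.9; and 23.4 − (650 + 1,030)/120 = 9.4.

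| f | By randomised group | Dropped | Moved |
|---|---|---|---|
| 5% | 15.7 | 14.1 | 10.0 |
| 10% | 19.7 | 16.9 | 9.4 |
| 20% | 25.0 | 20.0 | 7.2 |

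If the clock for a moved participant starts at the injection and he takes the same 6.5 minutes, the result equals the dropped column. Entering 45 minutes for each switched participant still leaves the topical mean 0.6, 1.3 and 3.3 minutes below the uncapped mean at 5%, 10% and 20%. Every option errs in the same direction.

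**Rounding in the other direction.** Numbness is seen only when tested, so recorded onset is rounded up. I rounded simulated onsets up to the next multiple of 3 or 5 minutes (the run-in interval), kept those at or below 45, and compared their mean with the uncapped mean. At s = 0.5 the net error is +0.8 to +1.8 minutes at 2% failure, −0.3 to +0.7 at 5%, −2.0 to −1.0 at 10% and about −5.4 to −4.5 at 20%. At 10% with s = 0.35 it is −1.1 to −0.1. Rounding can therefore cancel the shortfall at 5% or below, and nearly so at 10% if onset times vary little. If both arms are tested at the same interval, most of it drops out of the arm comparison.

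**The case against.** A reader might infer that the plan expressly discards participants switched to injection. It does not: the missing-data sentence is generic, the choice of test is left to suit the endpoint, and a chi-squared test of the proportion numb would be permitted. The exclusion follows only from applying the general rules, and the detailed plan could still prevent it. That softens the wording. But the summary is the default unless departed from, and it offers nothing for these times.

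A reader might also infer that failures would be hidden. They would not. Section 3.2.2 also records potency and problems during anesthesia, and Section 9.2 will present differences between as-treated and intention-to-treat. The switch count should be visible, but seeing it does not correct the dwell time printed beside it.

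Nor do the documents support the view that the cream would come out ahead of injection. On their own figures, 15 to 45 minutes against 3 to 10, it stays slower.

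It is tempting to tie the harm to the minimum dwell time for service planning. Section 8.2 draws that from the closely tested run-in, not from the Section 9.2 comparison, and every participant is tested before the procedure starts. Likewise, no section plans to report a dwell time sufficient for a set share of participants, so no coverage claim can be made.

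Finally, the uncapped mean is hypothetical: some participants might never become numb, and no analysis can estimate onset beyond the cap. This limits the percentages to illustration. The arm comparison above does not need that mean as its yardstick.

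**Conclusion.** The concern holds in a limited form. The general rules of Section 9.2 would base topical dwell time mainly on participants in whom the cream worked, understating both that time and the topical-minus-injectable gap.

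The size depends on a failure rate the documents do not give, and on an assumed lognormal onset with a 45-minute cap. It is negligible near 2% failure, may be offset by test-time rounding at about 5%, and generally becomes material from about 10%. There the success-only mean is 8-13% low. With log-SD 0.5 and injectable onset at 6.5 minutes, the gap reads 16.9 or 9.4 minutes instead of 19.7. The investigators expect the cream to be adequate, so the low end may apply.

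This is one component of a secondary endpoint. The primary pain endpoint and its power are not affected by this point.

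**What to change.** In Section 9.2, or in the detailed analysis plan before any analysis, state for time to adequate anesthesia that:

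- the analysis is by randomised group, with every topical participant in the denominator;
- a switch to injection counts as adequate anesthesia not achieved with the assigned method. It is not missing data. Nor should it be treated as censoring, because a switch made when the cream seems to be failing is informative;
- the report gives the cumulative percentage adequately numb by fixed times up to the dwell cap (for example 15, 30 and 45 minutes), the median if at least half become numb, and the switch rate alongside;
- this replaces a t-test on successes only. Percentages at fixed times can be compared with the chi-squared tests and 95% confidence intervals already planned.

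In the three-record example this would read 0/3, 1/3 and 2/3 numb by 15, 30 and 45 minutes, a median of 35 minutes, and one switch in three.

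Confirm that application, test and switch times are eCRF fields. Section 13.1 lists only details of the anesthetic procedures.

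The cost is a few sentences and one extra table, with no added participants or procedures. The downside is a slightly less favourable topical dwell time.
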